## Abstract

**Background/Objectives**: Multidisciplinary approaches spanning the physical, cognitive, and social domains of geriatric evaluation are essential to promote functional well-being and reduce the aversive consequences of aging. The main objective of the pilot study, “Multidomain Interventions to improve the COgnitive and fUNctional well-being of elderly individuals in residential sTructures” (I-COUNT), is to assess the feasibility of a 6-month multidomain intervention performed on older adults in Long-Term Care Facilities (LTCFs), compared with a group of residents following a traditional care approach. **Methods**: The intervention will involve two LTCFs in Italy and will include physical exercise and cognitive training, administered and monitored using wearable technologies, a nutritional program based on the Mediterranean diet enriched with selected functional foods, and the administration of the vaccinations recommended in the national vaccination plan. The I-COUNT study will assess the feasibility and acceptability of the defined protocol and provide information to determine the sample size for a definitive study. In relation to the potential health impact of multidomain interventions on older people living in LTCFs, the primary outcome will consider the change in microbiota composition assessed 3 months after the start of interventions, while secondary outcomes will include the evaluation of changes in selected biomarkers, physical performance, psychological health, cognitive functioning, and nutritional status at 6- and 9-month follow-up points. **Conclusions**: The I-COUNT study will allow us to assess the feasibility of delivering a multidomain intervention on elderly people. Exploratory findings on potential health effect will support the development of a larger-scale randomized controlled trial. **Trial registration number**: ClinicalTrials.gov ID NCT06820710.

## 1. Introduction

The demographic changes in recent decades have led to a significant increase in the proportion of older adults, with projections suggesting that by 2050, 16% of the global population will be aged 65 and older [1]. This trend affects many countries, particularly Italy, which has one of the highest proportions of older people in Europe, with individuals aged ≥65 years accounting for approximately 24% of the population in 2024, up from 21.5% in 2014 [2]. In this context, aging and age-related diseases represent a growing challenge for individuals, for families, and for social, economic, and health systems [3].

The consequences of aging are heterogeneous, often including a combination of clinical and subclinical conditions that contribute to frailty and diminished independence. Geriatric syndromes—multifactorial clinical conditions that do not fall into defined disease categories—result from the accumulation of impairments across multiple systems, making older adults particularly vulnerable to situational challenges [4]. This evidence underscores the multiple healthcare needs of older adults [5] and highlights the importance of identifying and adopting preventive approaches [6]. Recent studies from the “Finnish Geriatric Intervention Study to Prevent Cognitive Impairment and Disability” (FINGER) network, an international research initiative that promotes and tests multidomain lifestyle interventions aimed at preventing cognitive decline and dementia in older adults, emphasize the critical role of multidisciplinary interventions involving several specialists to provide older individuals with the most comprehensive care. These interventions address various domains of geriatric assessment, including cognitive, social, and physical aspects [7,8]. The results are encouraging, as they show that the elderly population at risk of cognitive decline benefits from multidomain lifestyle interventions, regardless of baseline characteristics [9]. Furthermore, implementing person-based approaches is essential for identifying and strengthening strategies that preserve their integrity and, most importantly, their autonomy [10].

Given these premises, particular attention should be directed to non-hospital settings, such as Long-Term Care Facilities (LTCFs), which are increasingly responsible for caring for older people across different age groups. LTCFs offer a variety of medical and personal care services to those who cannot live independently or need some type of long-term care support. To ensure successful aging, studies have been conducted to evaluate the effectiveness of physical and cognitive stimulating programs, along with nutritional interventions, aimed at preventing or mitigating frailty and disability. In particular, resistance training, combined with balance exercises, seems to prevent the deleterious effects of sarcopenia—the loss of muscle mass and strength—which is an age-related progressive condition, closely associated with the development of frailty [11,12]. Physical exercise training is also effective in improving cognitive status, physical function, and overall quality of life [13]. Similarly, dietary recommendations that align with the Mediterranean diet, emphasizing appropriate protein and caloric intake, are particularly beneficial for frail patients. In addition, the use of functional foods, containing probiotic strains and/or nutraceuticals, has demonstrated significant health benefits, contributing to disease prevention and supporting therapy [14]. Cognitive stimulation is highly recommended for people at risk of developing dementia and more generally for those in the early stages of cognitive decline. This intervention aims to improve cognitive function, enhance quality of life, and slow the progression of the disease [15]. Finally, vaccination programs are particularly important in comorbid and frail patients, as they help improve overall quality of life by reducing the risk of infections and their associated complications [16,17].

Despite these positive outcomes, the available studies often exhibit significant heterogeneity, both in terms of the population involved and the methods used to deliver the various interventions. Additionally, the feasibility and acceptability of a multidomain intervention—particularly one that incorporates new technologies to deliver and monitor these interventions among older adults residing in LTCFs—remain unclear [8].

In order to test the feasibility of a multidisciplinary intervention in older individuals living in residential structures and explore its potential effects, we designed the “Multidomain Interventions to improve the COgnitive and fUNctional well-being of elderly individuals in residential sTructures” (I-COUNT) protocol. This intervention includes a combination of selected physical activities and cognitive training, which will be administered and monitored through new technologies. In fact, physical activities have been shown to improve muscle mass, strength, and also cognition and mood, in particular among frail older adults [18,19,20]. Furthermore, cognitive training, in particular when based on new technologies and adapted to individual abilities, has been linked to improvement in memory, attention and executive functioning [21,22]. Additionally, the protocol incorporates a dietary intervention also including functional foods; dietary interventions based on the Mediterranean diet enriched with functional foods have been linked to anti-inflammatory and neuroprotective effects, contributing to gut and brain health [23,24,25]. Finally, the administration of vaccines in line with the National Vaccination Plan is suggested; in fact, vaccinations can be essential for prevention in frail populations and have been shown to reduce hospitalization and mortality in LTCFs [26,27,28]. The multidomain intervention will last 6 months and will be compared with the standard care adopted in the same LTCFs. This study is designed as a pilot and feasibility trial to evaluate whether the proposed multidomain intervention can be successfully implemented in LTCFs and to identify the necessary adaptations for a future large-scale, randomized, controlled trial. The potential health impact of multidomain interventions on older people living in LTCFs will be preliminarily evaluated considering the effect on microbiota composition and the differences in cognitive, nutritional and anthropometric status, psychological health, physical activity levels, and specific biomarkers between the intervention and control groups. Finally, we will also explore the potential impact of the multidomain intervention on participants’ perceived quality of life, as a secondary outcome.

## 2. Materials and Methods

The I-COUNT project is supported by the Italian National Recovery and Resilience Plan (PNRR) under the EU’s Next Generation EU (NGEU) program, within the Age-It initiative, which focuses on developing innovative approaches to mitigate frailty and prevent functional and cognitive decline in older adults (https://ageit.eu/wp/en/ (accessed on 16 April 2025)). Age-It identifies the most relevant challenges (e.g., demographic, biological, clinical, socio-economical, technological, and political), each of them addressed in a specific spoke. In particular, Spoke 8 of the Age-It project includes six work packages, three of which will focus on intervention studies targeting older adults in three different settings (community, hospital, and LTCF), while the other three are dedicated to the development and enhancement of technological solutions and tools to support intervention delivery, data management, and cost-effective analyses.

### 2.1. Study Design

The pilot study will follow a parallel group cluster randomized controlled trial. Randomization will be carried out at the cluster level to minimize the risk of contamination, and clusters will be defined as distinct units within LTCF residencies (i.e., separate floors or buildings, not sharing common areas or group activities, with minimal social interactions between clusters). A 6-month multicomponent intervention will be delivered and compared with usual care. Participants assigned to the multicomponent intervention will receive a 6-month program including Mediterranean diet and functional foods, physical exercise, and cognitive stimulation (see Multidomain intervention section). Participants in the intervention group will also be offered vaccinations according to the national vaccination calendar. The study protocol will include baseline evaluations (T0), a 6-month multidomain intervention, and follow-up assessments at 3 months (T1), 6 months (T2), and 9 months (T3). Participants in the control group will continue the standard care provided in their respective LTCFs, including their usual physical and cognitive stimulation activities, as well as their usual diet. Participants assigned to the control group will receive general information on healthy lifestyle and health, including risk factors. Figure 1 shows the flow diagram of the I-COUNT study protocol.

This protocol was designed in accordance with the CONSORT guidelines for feasibility and pilot studies. See the online Supplementary Materials for the CONSORT checklist figure. Participants or the public were not involved in the design of the study protocol.

### 2.2. Recruitment Process

Participants will be recruited from two Italian LTCFs: AltaVita-IRA (Padova, Italy) and Azienda Speciale Cremona Solidale (Cremona, Italy). In this pilot phase, the two participating LTCFs were selected based on established partnerships from previous collaborative research projects. Residents of the LTCFs will be recruited according to specific inclusion criteria: age ≥70 years; both sexes; residence in the identified LTCFs for at least 6 months; ability to communicate and collaborate with the research team; and Mini-Mental State Examination (MMSE) ≥18. The age threshold of 70 years was selected to focus on a population at greater risk of cognitive and functional decline, more representative of typical LTCF residents. The MMSE cut-off of ≥18 ensures the inclusion of participants with mild cognitive impairment, who retain sufficient cognitive capacity to engage in the multidomain intervention, while excluding individuals with moderate-to-severe dementia who may not safely or reliably participate in study procedures. Requiring a minimum 6-month stay in the LTCFs ensures that participants are well-adapted to the residential environment. Exclusion criteria include estimated length of stay in the LTCFs < 6 months; estimated life expectancy <6 months; previous gastrectomy or colectomy (due to potential interference with nutrient absorption and diet-related outcomes); percutaneous endoscopic gastrostomy (PEG) or nasogastric tube feeding; dysphagia; inability to undergo psychometric tests for any reason; history of psychiatric illness according to clinical anamnesis; and inability to walk, which could preclude safe participation in the physical activity component of the intervention. For each LTCF, residents will be screened for eligibility in collaboration with the facility’s staff, and eligible individuals will be invited to participate through structured in-person meetings. A total of 120 residents will be recruited, with 60 participants receiving the multidomain intervention and the remaining 60 participants assigned to the control group.

#### 2.2.1. Sample Size

The endpoint related to sample size refers to changes in gut microbiota composition between the two groups (multidomain intervention; control) assessed at 3-month follow-up compared to baseline. As suggested by Sim and Lewis to maximize precision and efficacy for pilot studies [29], a sample size of 30 individuals in the intervention group and 30 individuals in the control group is planned for each participating LTCF. This resulted in a total of 60 participants per group (120 in total). This allows for the detection of an effect size of 0.52 with 80% power and alpha = 0.05, considering a simplified approach assuming a two-sample *t*-test with equal variance (PASS 2024, version 24.0.1).

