#### 2.2.2. Randomization and Blinding

Two LTCFs will participate in the I-COUNT study, and within each LTCF, two units (floors or flats) will be randomly assigned to either the intervention or control group using the SAS Plan procedure. Participants will not be informed of their group allocation until the completion of the baseline assessment. Outcome evaluators will be blinded to participants’ group assignments, and participants will be instructed not to disclose this information to the assessors. The geriatricians and neuropsychologists responsible for developing the training activities will be different from the outcome assessors. If maintaining blinding for the outcome assessors is not feasible, additional assessors will be recruited to ensure impartiality.

Data will be processed in accordance with the European Regulation on the use of personal data (679/2016) and Legislative Decree no. 196 ss.ii. 30 June 2003, as amended by Legislative Decree no. 101 of 10 August 2018, as well as Deliberation of the Privacy Guarantor no. 52 of 24 July 2008 and subsequent updates.

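### The stated 80% power at an effect of 0.52 holds only for 120 independent residents; the trial randomises four units, two per arm, and does not have that power

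*Protocol article*

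**What the plan says.** Section 2.1 describes a parallel-group cluster randomised trial: "Randomization will be carried out at the cluster level to minimize the risk of contamination". Section 2.2.2 gives the number of clusters: "within each LTCF, two units (floors or flats) will be randomly assigned to either the intervention or control group". Two facilities with two units each make four clusters, two per arm, and each facility contributes one unit to each arm.

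Section 2.2.1 ties the sample size to the microbiota endpoint: "The endpoint related to sample size refers to changes in gut microbiota composition between the two groups", measured at 3 months against baseline. The number itself comes from a cited recommendation for pilot studies: "a sample size of 30 individuals in the intervention group and 30 individuals in the control group is planned for each participating LTCF". The article continues: "This resulted in a total of 60 participants per group (120 in total"). It then states what this size achieves: "This allows for the detection of an effect size of 0.52 with 80% power and alpha = 0.05, considering a simplified approach". The same sentence names the test behind the figure, a t-test with equal variance.

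Section 2.7.3 plans mixed models with cluster as a random effect and treats p < 0.05 as statistically significant.

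**The concern.** The power figure belongs to a different design and a different test from those planned. A two-sample t-test with 60 per arm treats every resident as a separate piece of evidence. Here the treatment is assigned to units of about 30 people who live on the same floor or in the same building, and the planned model recognises this. The sample size section contains no design effect, no allowance for having only four clusters, and no allowance for loss to follow-up.

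What is at stake is how the microbiota result is read. Section 2.7.1 makes it the primary health outcome. A reader who trusts the 80% would take a non-significant result as evidence against an effect of 0.52, which the trial had little chance of detecting. The Discussion also says that effect sizes and variability from this pilot will feed the sample size of the later trial, so treating residents as independent could carry over into that calculation.

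**Working it through.** **Inputs from the article.** Two units per arm and 30 residents per unit (Sections 2.2.1 and 2.2.2); 60 per arm; effect 0.52 in standard-deviation units; alpha 0.05; target power 80%. Sidedness is not stated.

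**Assumption.** The article gives no ICC. The range 0 to 0.10 is used below.

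**Step 1: reproduce the stated figure.** For independent residents, SE = √(2/60) = 0.183. With a two-sided t-test on 118 degrees of freedom (df), power at 0.52 is 80.6% and the effect detectable with 80% power is 0.516, which rounds to 0.52. A one-sided test would give 88.2%, so the stated figure is two-sided, at resident level, with no loss.

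**Step 2: add clustering.** The design effect is DE = 1 + (30 − 1) × ICC. The standard error of the difference is SE = √(2 × DE / 60), and the effective number per arm is 60 / DE. For ICC 0.05, DE = 1 + 29 × 0.05 = 2.45, SE = √(4.9/60) = 0.286, and the effective number is 60 / 2.45 = 24.5.

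**Step 3: power at 0.52, two ways.**
- Normal approximation, design effect only: Φ(0.52/SE − 1.96). For ICC 0.05 this is Φ(1.819 − 1.96) = Φ(−0.141) = 44%.
- Noncentral t with noncentrality 0.52/SE and 4 clusters − 2 arms = 2 df, the reference distribution for a comparison of unit means.

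The detectable effect under the normal approximation is (1.960 + 0.842) × SE. Under 2 df it was found by simulating the noncentral t.

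| ICC (assumed) | DE | SE | Effective n per arm | Power, design effect only | Power, 2 df | Detectable effect, design effect only | Detectable effect, 2 df |
|---|---|---|---|---|---|---|---|
| 0 | 1.00 | 0.183 | 60.0 | 81% | 36% | 0.51 | 1.03 |
| 0.01 | 1.29 | 0.207 | 46.5 | 71% | 30% | 0.58 | 1.17 |
| 0.05 | 2.45 | 0.286 | 24.5 | 44% | 19% | 0.80 | 1.62 |
| 0.10 | 3.90 | 0.361 | 15.4 | 30% | 14% | 1.01 | 2.04 |

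If facility is also fitted, only 1 df remains and power at 0.52 is 18%, 16%, 12% and 9% down the same rows.

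**Step 4: how much clustering the stated figure tolerates.** Setting design-effect-only power to exactly 80% at 0.52 gives DE = 30 × (0.52/2.802)² = 1.034, so ICC = 0.034/29 ≈ 0.001.

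**Step 5: what happens if the t-test in the power sentence were actually run.** Its true two-sided error rate would be about 2 × [1 − Φ(1.96/√DE)], which is 8%, 21% and 32% for ICC 0.01, 0.05 and 0.10, against a nominal 5%. Resident-level power therefore cannot be recovered by ignoring the clusters in the analysis.

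**Step 6: attrition, a smaller effect.** With an assumed 15% loss and no clustering, 51 per arm remain and the detectable effect moves from 0.52 to 0.56.

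**The case against.** The strongest reply has four parts.

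- **The calculation is right for the test it names, and the article calls the approach simplified.** True: this is a correct calculation applied to the wrong design. But the sentence does not say that clustering is what was simplified away, or what that costs, and it still asserts that the sample size permits this detection.
- **The study is a pilot.** The 120 comes from a pilot rule, not from the power calculation, and the Discussion disclaims definitive testing of efficacy. This stands and limits the consequence: the feasibility aims, which are summarised descriptively, do not depend on the power sentence. It does not make the figure true, and Sections 2.7.1 and 2.7.3 still attach a primary health outcome and a significance threshold to it.
- **The relevant ICC may be small.** Each facility supplies one unit to each arm, so differences between facilities are balanced. Menus are described at facility level, and a change from baseline removes stable differences between units. These points are fair, and zero cannot be ruled out from the article. But what counts is variation between units in the change over 3 months, and Section 2.1 defines units as not sharing common areas or group activities. An ICC of 0.01 already brings power down to 71%.
- **The 2-df figures depend on a degrees-of-freedom method that the article does not state.** Also fair; that detail can sit in the analysis plan, and the 36% at ICC 0 comes wholly from this choice. The design-effect-only column does not depend on it and still falls below 80% at an ICC of about 0.001.

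**Conclusion.** The concern holds: the power statement is wrong for this design. The 80% at 0.52 is correct only for 120 independent residents with complete follow-up. With two units of 30 per arm and an assumed ICC of 0.01 to 0.10, power is 71% down to 30% when only the design effect is counted, and 30% down to 14% with 2 between-cluster df. The effect detectable with 80% power is 0.58 to 1.01 in the first case and 1.17 to 2.04 in the second. The exact values rest on the assumed ICC, equal units of 30 and the choice of df. The conclusion needs only an ICC above about 0.001, or a test that uses the between-cluster df. The feasibility objective and the number enrolled are not affected.

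**What to change.** Delete the power sentence in Section 2.2.1, or replace it with text such as:

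> Ignoring clustering, 60 residents per arm would detect a standardised effect of 0.52 with 80% power. With two units per arm and an assumed ICC of 0.01 to 0.10, the detectable effect is about 0.6 to 1.0 before allowing for the few between-cluster degrees of freedom, and about 1.2 to 2.0 with 2 degrees of freedom. The trial is not powered for the microbiota comparison.

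Then justify 120 by precision for the feasibility outcomes. As an illustration, with an assumed retention of 80% the 95% confidence half-width is 1.96 × √(0.8 × 0.2 / 120) = 7 percentage points ignoring clustering. With a design effect of 2.45 it is 7.2 × √2.45 = 11 points. That design effect corresponds to an ICC of 0.05, which is again an assumption and would need its own justification for retention.

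The cost is one paragraph and a less favourable figure. No residents are added, and the design and analysis model stay as they are.

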#### 2.2.2. Randomization and Blinding

Two LTCFs will participate in the I-COUNT study, and within each LTCF, two units (floors or flats) will be randomly assigned to either the intervention or control group using the SAS Plan procedure. Participants will not be informed of their group allocation until the completion of the baseline assessment. Outcome evaluators will be blinded to participants’ group assignments, and participants will be instructed not to disclose this information to the assessors. The geriatricians and neuropsychologists responsible for developing the training activities will be different from the outcome assessors. If maintaining blinding for the outcome assessors is not feasible, additional assessors will be recruited to ensure impartiality.

Data will be processed in accordance with the European Regulation on the use of personal data (679/2016) and Legislative Decree no. 196 ss.ii. 30 June 2003, as amended by Legislative Decree no. 101 of 10 August 2018, as well as Deliberation of the Privacy Guarantor no. 52 of 24 July 2008 and subsequent updates.

